### 2.2. Inclusion Criteria

Patients diagnosed with asthma, age older than 20 years and less than 75 years, with BMI greater than 25 kg/m^2^ will be included. All patients must have experienced one or more episodes of moderate or severe exacerbations in the previous year. Written informed consent for participation in the present study will be obtained from all patients.

### 2.3. Exclusion Criteria

Exclusion criteria are the following: aspartate aminotransferase or alanine aminotransferase greater than 100 IU/L; creatinine above 2.0 mg/dL; life-threatening arrhythmia or paroxysmal tachycardia with heart rate greater than 100 beats per minute; admitted for acute myocardial infarction or heart failure in the previous year; malignancy diagnosed in the previous 5 years, except for complete remission after treatment; macrolide antibiotic treatment in the previous 4 weeks; biologics including omalizumab, mepolizumab, benralizumab, and dupilumab in the previous 8 weeks at the start of azithromycin in the present study; QT interval requires correction for heart rate at more than 480 ms; pregnancy or breastfeeding; BMI less than 25 kg/m^2^; and ineligible for the present study as determined by the researchers.

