## 1. Introduction

Asthma is a common disease, and the majority of patients are well-controlled by treatment, including inhaled corticosteroids and bronchodilators, which are pivotal treatments for asthma [1,2]. However, approximately 5 to 10% of the patients are resistant to the standard treatments, and they are considered to have severe asthma [3]. Clinical phenotypes of severe asthma are heterogeneous, but recognized as symptomatic, with reduced pulmonary function, higher airway inflammation, and frequent exacerbations [4,5]. Exacerbation is one of the important events in severe asthma that is related to higher mortality, emergency hospital visits, increased medical costs, and lower quality of life [6,7,8]. Thus, better control exacerbations by treatment, along with exploring the severity mechanisms, are increasingly required. Recently, several biologics targeting molecules associated with eosinophilic inflammation such as interleukin (IL)-4, IL-5, IL-13, and immunoglobulin (Ig) E, called type 2 cytokines, have become available, and they have the capacity to provide control for some patients with severe asthma, especially those characterized by eosinophilic airway inflammation [9,10]. However, their efficacy is insufficient for patients with less or non-type 2 inflammation [11]. For such severe asthma patients without eosinophilic airway inflammation, exploring novel treatments and therapeutic targets is needed.

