### 2.4. Study Endpoints

The primary endpoint is reduction in the exacerbation rate after 48-week treatment with azithromycin compared to that before the intervention (Table 1). The asthma exacerbation rate is defined as the proportion of analyzed cases with asthma exacerbations after treatment. Secondary endpoints are differences in clinical and laboratory parameters between before and after azithromycin treatment, including the blood eosinophil ratio, eosinophil count, IgE, pulmonary functions such as vital capacity (VC), forced vital capacity (FVC), %VC, forced expiratory volume in one second (FEV_1_), FEV_1_%, and %FEV_1_, and weight, BMI, level of fractional exhaled nitric oxide (FeNO), and scores on the asthma control test. Other secondary endpoints are to clarify the characteristics of the frequency of asthma exacerbations in improving/non-improving patients, and the diversity indices of the gut microbiome including the Chao 1, Shannon, and Simpson indices. For other exploratory endpoints, height, weight, BMI, and the tendency for decreased exacerbations will be assessed at 24 weeks of azithromycin treatment. In addition, biomarkers including cytokines, chemokines, short-chain fatty acids, metabolomics, and species of the gut microbiome will be compared between before and after azithromycin treatment and examined for relationships between changes and exacerbation at 48 weeks. The effects of sex and age attenuating the effect of azithromycin on exacerbations will also be assessed, because sex and age have been shown to have great impacts on the incidence and pathophysiology of asthma and obesity [26,48,49,50].

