### 2.5. Clinical Data to Be Collected, including Adverse Events

The present study consists of 7 visits: before intervention, at azithromycin initiation, 4 weeks later, 12 weeks later, 24 weeks later, 36 weeks later, and 48 weeks later. Informed consent will be obtained at visit 1 with recording of clinical information including treatment contexts for asthma, smoking index, exacerbation times in the previous year, and comorbidities. Physical measurements, electrocardiogram, and blood examination will be evaluated at all visits except for visit 1 to monitor adverse effects of azithromycin. Pulmonary function testing, FeNO, and asthma control tests are to be performed at visits 2, 5, and 7. Biomarker analyses of blood, including multiplex assay of cytokines and chemokines (Eve Technologies, Calgary, AB, Canada), short-chain fatty acids, and metabolomics analysis (Kyusyu Pro Search, Fukuoka, Japan) are to be performed at visit 2 and visit 7. Gut microbiome analysis with 16s rRNA Sequencing (Massachusetts Host-Microbiome Center at the Brigham and Women’s Hospital, Boston, MA, USA) will be performed at visit 1 and visit 7. In terms of adverse effects of azithromycin, if the participants have any symptoms, physical and laboratory abnormalities of grade 2 level associated with azithromycin, the dose will be reduced to 250 mg 3 times per week. If the participants have any symptoms, physical and laboratory abnormalities of grade 3 level associated with azithromycin, administration of azithromycin will be terminated immediately.

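### Eosinophil, IgE, FeNO and cytokine baselines may be taken just over 8 weeks after a biologic, so any effect still present then and gone by week 48 would count as an azithromycin change

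*Protocol article*

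**What the plan says.** **Eligibility.** Section 2.3 of the protocol article excludes "biologics including omalizumab, mepolizumab, benralizumab, and dupilumab in the previous 8 weeks at the start of azithromycin in the present study". One window covers all the named drugs, and it is counted back from the first azithromycin dose.

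**What the drugs act on.** The Introduction describes "biologics targeting molecules associated with eosinophilic inflammation such as interleukin (IL)-4, IL-5, IL-13, and immunoglobulin (Ig) E".

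**Endpoints.** Section 2.4 lists as secondary endpoints "differences in clinical and laboratory parameters between before and after azithromycin treatment, including the blood eosinophil ratio, eosinophil count, IgE", and later in the same list "level of fractional exhaled nitric oxide (FeNO), and scores on the asthma control test". Cytokines and chemokines are compared before and after treatment as exploratory endpoints.

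**Timing of baseline.** Section 2.5 states "Pulmonary function testing, FeNO, and asthma control tests are to be performed at visits 2, 5, and 7", and that "blood examination will be evaluated at all visits except for visit 1". Table 1 agrees: visit 2 is the azithromycin start, and the blood biomarker panel is drawn at visits 2 and 7 only. IgE has no line of its own in the schedule. Its baseline is taken to be visit 2 because no blood examination is scheduled earlier.

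**Design and analysis.** Section 2.1 describes an open-label study with one arm. Section 2.8 compares the secondary laboratory parameters before and after treatment by paired t-tests or McNemar's tests.

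**The concern.** A paired comparison without a control group attributes the whole change between two visits to treatment. That requires the baseline to be a steady value for each patient. Section 2.1 argues that the before/after design removes differences between individuals. It does remove stable differences, but not a marker that is still moving after another drug has been stopped.

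The markers at issue belong to the pathway that the stopped drugs act on. For eosinophils and IgE this follows from the Introduction. That FeNO and some of the cytokines follow the same inflammation is the usual reading, but the article does not state it.

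An eligible patient may reach visit 2 just over 8 weeks after the last dose. If a biologic effect remains then and has gone by week 48, its disappearance is added to the azithromycin change. It could mask a real change, reverse it or produce one that is not there. Visit 2 is also the only scheduled measurement before treatment, so the data cannot show whether a marker was already drifting.

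**Working it through.** The plan has no figure of its own on this point to reproduce. The check has three steps, and everything numerical in steps 2 and 3 rests on assumptions.

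**Step 1: the passages side by side.**
- Earliest permitted entry: just over 8 weeks after the last biologic dose (Section 2.3).
- Baseline measurement: the same visit to which those 8 weeks are counted (Section 2.5, Table 1).
- Final measurement: 48 weeks later, so about 8 + 48 = 56 weeks after that dose.
- Comparator: none (Section 2.1).
- Test: paired, with no adjustment or subgroup by prior biologic use described (Section 2.8).

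Nothing in this sequence separates a fading biologic effect from an azithromycin effect.

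**Step 2: how much effect could fade between the two visits.** Assume exponential decay, with fraction remaining = 0.5^(weeks / half-life of effect). The article gives no half-life; 2 to 12 weeks is an assumed range.

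| Assumed half-life of effect | Remaining at 8 weeks | Remaining at 56 weeks |
|---|---|---|
| 2 weeks | 6% | 0% |
| 4 weeks | 25% | 0% |
| 8 weeks | 50% | under 1% |
| 12 weeks | 63% | 4% |

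Under each assumption, nearly all of what is left at baseline disappears before visit 7, provided that no biologic is given in between.

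**Step 3: what that does to the paired test.** Let a share f of patients drift by D, in units of the SD of the paired change, with a true azithromycin effect of zero. The bias in the mean change is f × D. With n = 44 (the required number in Section 2.6), a two-sided 5% paired t-test was simulated 20,000 times for each combination.

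| Share f (patients out of 44) | Drift D | Bias f × D | False-positive rate |
|---|---|---|---|
| 0% | none | 0 | 5% |
| 5% (2.2) | 0.5 SD | 0.025 SD | 5.4% |
| 5% (2.2) | 1 SD | 0.05 SD | 6.3% |
| 10% (4.4) | 0.5 SD | 0.05 SD | 5.8% |
| 10% (4.4) | 1 SD | 0.10 SD | 9.4% |
| 20% (8.8) | 0.5 SD | 0.10 SD | 10% |
| 20% (8.8) | 1 SD | 0.20 SD | 22% |

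Hand check of the last row: the standardised shift is √44 × 0.20 / √(1 + 0.2 × 0.8 × 1²) = 1.327 / 1.077 = 1.23. The normal approximation then gives P(Z > 1.96 − 1.23) ≈ 23%, close to the simulated 22%.

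More extreme inputs give higher rates (53% at f = 20% and D = 2 SD). Nothing in the article suggests such inputs, and they are not relied on.

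**The case against.** The strongest objection is that carry-over is only possible, not shown. The sponsor has already set a washout and counts it to the visit at which baseline is measured. The article says nothing about how long these drugs act or how many participants will have had one. The study is motivated by disease with little or no eosinophilic inflammation, where the Introduction calls biologics insufficient, so recent users may be few. At a share of 5% to 10% and a drift of 0.5 SD, the false-positive rate is 5.4% to 5.8%, which hardly matters. This all stands, and it is why the point is conditional.

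A second objection is that a last-dose date and a sensitivity analysis are details for the case report form and the analysis plan, neither of which is shown. This stands in part: their absence from a condensed article is no fault in itself, and Section 2.5 does record asthma treatment history at visit 1. But the exposure comes from choices that the article fixes: the 8-week window, a single pre-treatment measurement at azithromycin start, and a paired test with no control. A later analysis plan can deal with it only if the time since the last dose has been recorded.

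A reader might infer more than the documents support:
- That drift will occur. The duration of effect is not given.
- That week 48 is free of biologic effect. Section 2.1 does not say whether a biologic may be started during the 48 weeks.
- That IgE will show a false fall. The Introduction names IgE as a target but gives no direction of change after stopping.
- That eosinophils would recover fully from suppression between the visits. If effect followed residual drug, only the fraction still present at visit 2 could be lost.

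**Conclusion.** The point holds in conditional form. Any biologic effect present at visit 2 and absent at week 48 would be counted as an azithromycin change in eosinophil ratio and count, FeNO, the cytokine panel and, by inference, IgE. The direction can be either way.

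On assumed shares of 5% to 20% of patients and drifts of 0.5 to 1 SD, the false-positive rate of the nominal 5% paired test lies between about 5.4% and 22%. The simulation describes the paired t-test planned for the secondary markers. For the cytokine panel, Section 2.8 names no before/after test, so only the bias argument carries over. If few patients had a recent biologic, or the effect has gone by 8 weeks, the problem is negligible.

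This is a cheap improvement to secondary and exploratory marker comparisons. It is not an error in the plan, and nothing here is claimed about the primary endpoint.

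**What to change.** 1. At visit 1, record with the asthma treatment history which biologic was last given and the date of the last dose. Also record any biologic started during the 48 weeks, so that it is known whether the week 48 value is free of one.
2. Prespecify that the before/after comparisons of eosinophil ratio and count, IgE, FeNO and the cytokine panel are reported twice: in all analysed patients, and without patients who had a recent biologic. The sponsor should set and justify the look-back period before the data are seen.
3. State that a change in these markers is attributed to azithromycin only if it holds in the second analysis. Judge this by the estimate and its confidence interval, since the second analysis has fewer patients.

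The eligibility washout, enrolment and the primary analysis stay as they are.

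The cost is a few data items, one analysis rule and some precision in these comparisons. On the assumed shares, removing 5% or 20% of 44 leaves about 42 or 35 patients. With an unchanged SD, the standard error grows by √(44/42) = 1.02 or √(44/35) = 1.12, that is by about 2% or 12%. If there are almost no recent users, the two analyses will nearly coincide, which is itself worth reporting.

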### 2.4. Study Endpoints

The primary endpoint is reduction in the exacerbation rate after 48-week treatment with azithromycin compared to that before the intervention (Table 1). The asthma exacerbation rate is defined as the proportion of analyzed cases with asthma exacerbations after treatment. Secondary endpoints are differences in clinical and laboratory parameters between before and after azithromycin treatment, including the blood eosinophil ratio, eosinophil count, IgE, pulmonary functions such as vital capacity (VC), forced vital capacity (FVC), %VC, forced expiratory volume in one second (FEV_1_), FEV_1_%, and %FEV_1_, and weight, BMI, level of fractional exhaled nitric oxide (FeNO), and scores on the asthma control test. Other secondary endpoints are to clarify the characteristics of the frequency of asthma exacerbations in improving/non-improving patients, and the diversity indices of the gut microbiome including the Chao 1, Shannon, and Simpson indices. For other exploratory endpoints, height, weight, BMI, and the tendency for decreased exacerbations will be assessed at 24 weeks of azithromycin treatment. In addition, biomarkers including cytokines, chemokines, short-chain fatty acids, metabolomics, and species of the gut microbiome will be compared between before and after azithromycin treatment and examined for relationships between changes and exacerbation at 48 weeks. The effects of sex and age attenuating the effect of azithromycin on exacerbations will also be assessed, because sex and age have been shown to have great impacts on the incidence and pathophysiology of asthma and obesity [26,48,49,50].

### 2.5. Clinical Data to Be Collected, including Adverse Events

The present study consists of 7 visits: before intervention, at azithromycin initiation, 4 weeks later, 12 weeks later, 24 weeks later, 36 weeks later, and 48 weeks later. Informed consent will be obtained at visit 1 with recording of clinical information including treatment contexts for asthma, smoking index, exacerbation times in the previous year, and comorbidities. Physical measurements, electrocardiogram, and blood examination will be evaluated at all visits except for visit 1 to monitor adverse effects of azithromycin. Pulmonary function testing, FeNO, and asthma control tests are to be performed at visits 2, 5, and 7. Biomarker analyses of blood, including multiplex assay of cytokines and chemokines (Eve Technologies, Calgary, AB, Canada), short-chain fatty acids, and metabolomics analysis (Kyusyu Pro Search, Fukuoka, Japan) are to be performed at visit 2 and visit 7. Gut microbiome analysis with 16s rRNA Sequencing (Massachusetts Host-Microbiome Center at the Brigham and Women’s Hospital, Boston, MA, USA) will be performed at visit 1 and visit 7. In terms of adverse effects of azithromycin, if the participants have any symptoms, physical and laboratory abnormalities of grade 2 level associated with azithromycin, the dose will be reduced to 250 mg 3 times per week. If the participants have any symptoms, physical and laboratory abnormalities of grade 3 level associated with azithromycin, administration of azithromycin will be terminated immediately.

### 2.6. Sample Size

A previous study reported that the incidence rate ratio of asthma exacerbations for azithromycin compared to placebo was approximately 0.6 [36], but the current participants have obesity, which is estimated to reduce the attenuation effect due to the pharmacological differences between lean and obese individuals [51,52]. Thus, we anticipate an incidence rate ratio of 0.9 with azithromycin and set the expected exacerbation rate after intervention at 90%, with the exacerbation rate before the intervention set at 100%. Based on the normal approximation of the binomial distribution with a significance level of 5% and power of 90%, 44 patients are required. Thus, the target sample size was set at 50 patients considering dropouts.

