### 2.8. Statistical Analysis

The primary and secondary endpoints and safety will be assessed in all patients completing 48 weeks of treatment. Then, patients without necessary exacerbation data for analysis or who withdrew consent before treatment will be excluded. For the primary endpoint, the asthma exacerbation rate at 48 weeks and its two-sided 95% confidence interval (CI) will be estimated with the normal approximation. The asthma exacerbation rate difference between pre- and post-treatment will also be tested binomially. For the clinical laboratory parameters and the diversity indices of the gut microbiome at pre-treatment and post-treatment as secondary endpoints, paired *t*-tests or McNemar’s tests will be used. The chi-squared test will be used to investigate the characteristics related to the frequency of asthma exacerbations. For other exploratory endpoints, height, weight, BMI, and tendency for an attenuation of the exacerbation rate at 24 weeks will be assessed by paired *t*-tests. Univariate analysis and multivariate analysis with a logistic regression model, adjusting BMI and body weight, will be performed to evaluate the relationships between the changes (improvement or no improvement in biomarker changes) and asthma exacerbation at 48 weeks.

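### The entry criterion fixes the pre-treatment exacerbation proportion at 100%, so the primary pre/post test cannot separate a drug effect from selection and regression to the mean

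*Protocol article*

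**What the plan says.** Four statements in the protocol article combine.

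- Section 2.2, entry: "All patients must have experienced one or more episodes of moderate or severe exacerbations in the previous year".
- Section 2.4, endpoint: "The primary endpoint is reduction in the exacerbation rate after 48-week treatment with azithromycin compared to that before the intervention". The rate is a yes/no proportion: "The asthma exacerbation rate is defined as the proportion of analyzed cases with asthma exacerbations after treatment".
- Section 2.6, planning values: "set the expected exacerbation rate after intervention at 90%, with the exacerbation rate before the intervention set at 100" per cent. Then: "Based on the normal approximation of the binomial distribution with a significance level of 5% and power of 90%, 44 patients are required", and "the target sample size was set at 50 patients considering dropouts".
- Section 2.8, analysis: "the asthma exacerbation rate at 48 weeks and its two-sided 95% confidence interval (CI) will be estimated with the normal approximation", followed by "The asthma exacerbation rate difference between pre- and post-treatment will also be tested binomially".

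There is no control arm. The limitations paragraph of the Discussion concedes the missing placebo group and says that triggers may differ before and after treatment. It mentions neither selection on a past exacerbation nor regression to the mean. No untreated recurrence proportion is given anywhere.

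**The concern.** A baseline proportion that equals 100% because of an inclusion rule has no variance and can move in one direction only. Patients chosen because they had an event last year will not all have one in the next 48 weeks, treated or not. The follow-up is also shorter than the one-year look-back, which pushes the same way. A significant fall below 100% is thus expected under many plausible conditions with an inert drug, yet the Conclusions present the study as evaluating the effect of azithromycin on exacerbations. At stake is whether a positive primary result can be read as efficacy.

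**Working it through.** **The plan's own figure.** With p0 = 1.00, p1 = 0.90, 5% level and 90% power, the one-sample normal approximation is n = [z_a·√(p0(1−p0)) + z_b·√(p1(1−p1))]² / (p0−p1)². The null variance is zero, so n = (1.2816 × 0.3)² / 0.01 = 14.8, i.e. 15. Using the variance at 0.90 throughout gives 95 (two-sided) or 78 (one-sided). The rule that one exacerbation-free patient rejects needs 22 patients for 90% power. None of these gives 44. This is a separate defect. It matters here because the sample size does not reveal which test is meant, so three readings are carried forward.

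**Rejection rules at n = 44** (x = number of exacerbation-free patients).

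- Fixed 100%: one such patient is impossible under the null, so x ≥ 1 rejects.
- Wald 95% CI excluding 100%: at x = 3, 0.932 + 1.96√(0.932 × 0.068/44) = 1.006; at x = 4, 0.909 + 1.96√(0.909 × 0.091/44) = 0.994. So x ≥ 4.
- Exact McNemar, all discordant pairs one way: 2 × 0.5⁵ = 0.0625; 2 × 0.5⁶ = 0.031. So x ≥ 6.

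**Chance that an inert drug is declared effective, by untreated 48-week proportion p** (binomial tail with probability 1 − p, n = 44).

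| p | Fixed 100% | Wald CI | Exact McNemar |
|---|---|---|---|
| 95% | 1 − 0.95⁴⁴ = 89.5% | 17.7% | 2.2% |
| 90% | 99.0% | 65.3% | 27.4% |
| 85% | 99.9% | 91.3% | 66.4% |
| 80% | >99.9% | 98.5% | 89.8% |
| 70% | >99.9% | >99.9% | 99.7% |

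With n = 50 the figures are higher: at p = 90% they are 99.5%, 75.0% and 38.4%.

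**What p might be (assumption).** Exacerbations are taken as gamma-Poisson in the source population before selection, with mean λ = 0.5, 1, 1.5, 2 or 3 per year and shape θ = 0.5, 1, 2 or infinity (20 scenarios). Follow-up is T = 48/52 year and the drug has no effect. With P0(t) = (1 + tλ/θ)^(−θ), or e^(−λt) when θ is infinite:

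p = [1 − P0(1) − P0(T) + P0(1+T)] / [1 − P0(1)].

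Examples: λ = 1, θ = 1 gives (1 − 0.500 − 0.520 + 0.342)/0.500 = 0.644. With Poisson counts the formula reduces to 1 − e^(−λT): 0.603, 0.842 and 0.937 for λ = 1, 2 and 3.

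| Mean per year | p, untreated | Fixed 100% | Wald CI | Exact McNemar |
|---|---|---|---|---|
| 0.5 | 37–53% | >99.9% | >99.9% | >99.9% |
| 1 | 60–67% | >99.9% | >99.9% | at least 99.9% |
| 1.5 | 73–75% | >99.9% | at least 99.8% | 98–99% |
| 2 | 78–84% | >99.9% | 93–99% | 71–95% |
| 3 | 83–94% | 94% to >99.9% | 30–96% | 5.5–80% |

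In 19 of the 20 scenarios p lies below 90%. The exception is Poisson with mean 3, at 94%.

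**Does a pre/post rate ratio escape the problem?** No. For an inert drug the annualised ratio after selection is 1 − E[Λe^(−Λ)]/λ, where Λ is a patient's own yearly rate. For Poisson this is 1 − e^(−λ): 0.39 at λ = 0.5 and 0.95 at λ = 3. Those are also the extremes of the 20 scenarios.

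**The case against.** The case for the plan has four parts.

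- Section 2.8 puts estimation first; the test is an addition. This stands: the 48-week proportion and its interval stay usable if set against an external benchmark. A reader might infer that a positive result carries no information at all. That goes too far; the test and the causal reading fail, not the estimate.
- The wording of the test is loose, and the untreated recurrence is unknown. This also stands. A reader might infer that an inert drug would be declared effective almost every time. That holds for the fixed-100% reading across the assumed scenarios, but not for the Wald or McNemar readings at high event rates. Section 2.1 defines moderate exacerbations broadly, including increased reliever use over at least two days, so high rates cannot be ruled out.
- A reader might also infer that the planned 90% is necessarily no better than an ineffective drug would show. This holds in 19 of 20 scenarios, not all.
- The missing placebo arm is disclosed, and the single-arm design is justified by microbiome diversity. The disclosure is general and does not name the selection effect. The microbiome rationale concerns secondary and exploratory endpoints and gives no support to a 100% null for the primary one.

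That a separate analysis plan may add detail does not answer the point, because the endpoint definition, the null value and the test are all stated in the article.

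**Conclusion.** The point holds. Sections 2.2, 2.4, 2.6 and 2.8 together make the baseline 100% by construction, and no control or benchmark separates drug effect from regression to the mean. This needs no assumption. The size of the error does need some: the untreated recurrence proportion and the reading of the test. In the assumed scenarios, inert-drug rejection at n = 44 is at least 94% against a fixed 100%, and about 98% or more under every reading for means up to 1.5 per year. It is 71% to 99% across the Wald and McNemar readings at a mean of 2, and 5.5% to 96% at a mean of 3. It approaches the nominal 5% only where nearly all untreated patients would relapse and a stricter reading of the test applies.

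**What to change.** 1. Delete the test against 100% and make no efficacy claim from the fall below it.
2. Make the primary analysis estimation: the 48-week proportion with an exacerbation and its 95% CI. Read it against a pre-specified, justified untreated recurrence proportion for patients selected on at least one prior-year exacerbation. State the source, a range and the limits of transferability. The placebo arm of the cited randomised trial is one candidate, but the Introduction calls that trial's participants largely different.
3. Report the within-patient pre/post rate ratio per patient-year as supportive only, not tested against 1. Prior-year counts are already recorded at visit 1.
4. Restate Section 2.6. The 90% power for 90% versus 100% is not power to detect a drug effect. Give precision instead: at n = 44 the half-width is 1.96√(0.84 × 0.16/44) = 0.108 to 1.96√(0.60 × 0.40/44) = 0.145, about ±11 to ±14 percentage points.
5. Reword the objective, limitations and conclusion so that the pre/post fall is described as drug effect plus regression to the mean.

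Cost: no new visits or data collection, one benchmark to source, and a weaker, estimation-only claim. A powered decision rule is out of reach at this size. Keeping the planned ratio of 0.9 (one-sample normal approximation, two-sided 5%, 90% power), 80% versus 72% needs [1.96√(0.80 × 0.20) + 1.2816√(0.72 × 0.28)]²/0.08² ≈ 289 patients, and 60% versus 54% about 710.

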The present study is a multi-center, prospective, single-arm intervention study involving treatment with azithromycin for 48 weeks to clarify whether such treatment reduces exacerbations of obesity-induced severe asthma. To explore the mechanism, the gut microbiome, metabolites produced by microbes such as short-chain fatty acids, and blood inflammatory cytokines will be assessed to evaluate their correlation with the reduction in exacerbations by azithromycin in obesity-induced severe asthma. Importantly, the present study is designed as a single-arm intervention considering the gut microbiome and biomarker diversity of individuals, which allows us to avoid individual diversity at baseline and explore specific microbes and biomarkers associated with clinical outcomes with a relatively small sample size, taking into account ethical concerns. Compared to the AMAZES study mentioned above, the study design, participants, intervention dose of azithromycin, and study endpoints are largely different. Briefly, the present study is planned as a single-arm intervention study compared to a randomized, double-blinded, placebo-controlled trial in the AMAZES study because of the sample size calculation considering gut microbiome diversity of individuals set as secondary endpoints. As study participants, the present study targets Japanese asthmatic patients with obesity (BMI > 25 kg/m^2^) compared to asthma patients recruited in Australia and New Zealand regardless of their BMI in the AMAZES study. Considering efficacy and safety, the intervention dose of azithromycin is 250 mg per day in the present study compared to 500 mg, 3 times per week in the AMAZES study. Finally, the present study focuses on the gut microbiome and its metabolism as study endpoints. The present results will contribute to developing new therapies for obesity-induced severe asthma and identify targeted microbes or molecules associated with the regulation of asthma with obesity.

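### The 44 patients stated for 90% power do not follow from the stated inputs, and 90% is the power of neither primary analysis

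*Protocol article*

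**What the plan says.** Section 2.6 starts from a published azithromycin-versus-placebo incidence rate ratio of about 0.6 and weakens it for obesity: "we anticipate an incidence rate ratio of 0.9 with azithromycin". It then moves to proportions: "set the expected exacerbation rate after intervention at 90" per cent, "with the exacerbation rate before the intervention set at 100" per cent. The result is "Based on the normal approximation of the binomial distribution with a significance level of 5% and power of 90%, 44 patients are required", raised to 50 for dropouts. Whether the 5% is one- or two-sided is not stated.

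Three other sections bear on this:

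- Section 2.2 (Inclusion Criteria) admits only patients with at least one moderate or severe exacerbation in the previous year, so the 100% is fixed by eligibility.
- Section 2.4 (Study Endpoints) defines the exacerbation rate as a proportion of patients.
- Section 2.8 (Statistical Analysis) names two analyses of the primary endpoint: the 48-week rate with a two-sided 95% confidence interval by normal approximation, and a binomial test of the pre/post difference.

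**The concern.** The inputs, the method and the answer are all printed, so a reader should be able to get from one to the other. At a null proportion of exactly 100% the binomial variance is zero, which is where a normal approximation cannot be used, so a figure of 44 needs explaining. The calculation is the only numerical support for the trial's size on its primary endpoint. If 44 does not follow, and if 90% is the power of neither analysis in section 2.8, the article gives no valid statement of what the trial can show. The effect size is also doubtful, because a ratio of event rates between two treatments has been used as a ratio of patient proportions before and after one treatment.

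**Working it through.** **Inputs (section 2.6).** p0 = 1.0, p1 = 0.9, difference d = 0.1, significance 5%, power 90%. Normal quantiles: 1.960 two-sided or 1.645 one-sided for significance, 1.2816 for power.

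**1. Trying to reproduce 44.** The one-sample formula is n = (z_α√[p0(1−p0)] + z_β√[p1(1−p1)])² / d².

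- As stated: the first term is zero, so n = (1.2816 × 0.3 / 0.1)² = 14.8, that is **15**. The significance level and its sidedness drop out.
- With continuity correction, n' = (n/4)(1 + √[1 + 2/(nd)])² = 23.7, that is **24**.
- Alternative variance in both terms: (1.960 + 1.2816)² × 0.09 / 0.01 = 94.6, that is **95** two-sided; with 1.645 it is 77.1, that is **78** one-sided.
- Variance at the average, 0.95, in the null term: **56** one-sided, **66** two-sided.
- Exact binomial against 100%: one exacerbation-free patient rejects, so 1 − 0.9ⁿ ≥ 0.90 gives n ≥ ln 0.1 / ln 0.9 = 21.9, that is **22**.

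None of these gives 44.

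**2. Where 44 can come from.** Take 90% as the null and 100% as the alternative, two-sided. Then n = (1.960 × 0.3 + 1.2816 × 0)² / 0.01 = 34.57, and the continuity correction turns this into (34.57/4)(1 + √[1 + 2/3.457])² = 44.005. The z_β term is multiplied by zero, so the answer is the same whatever power is entered. The hypothesis tested would be a rate of 90%, not 100%. This may be the source, but the article does not say so.

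**3. Power of the named analyses at n = 44, true rate 90%.**

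- Binomial test against 100%: 1 − 0.9⁴⁴ = 1 − 0.0097 = **99.0%**.
- Two-sided 95% normal-approximation interval, with an upper limit below 100% counted as success (my assumption). With 40 patients exacerbating, 0.9091 + 1.960 × 0.0433 = 0.994, which excludes 100%. With 41, 0.9318 + 1.960 × 0.0380 = 1.006, which does not. So at least 4 exacerbation-free patients are needed, and P(X ≤ 40 | 44, 0.9) = **65.3%**. On this rule 90% power takes 65 patients.
- At n = 50 the two figures are 99.5% and 75.0%.

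**4. Rate ratio to proportion.** The article gives no event rate, so this is illustration only. Under a Poisson model with mean m events per period, a rate ratio of 0.9 leaves a proportion 1 − exp(−0.9m) with at least one event. For m = 1, 2 and 3 this is 59%, 83% and 93%. It equals 90% only when m = ln 10 / 0.9 = 2.56. So a rate ratio of 0.9 does not in general mean 90% of patients.

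**5. What 44 patients do give.** Exact (Clopper–Pearson) 95% intervals: 40/44 (90.9%) gives 78.3% to 97.5%, a half-width of about 10 points; 22/44 (50%) gives 34.6% to 65.4%, about 15 points.

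**The case against.** The strongest reply is that the error does no harm to the planned test. Against a null of 100%, 22 patients would be enough for 90% power and 44 give 99.0%, so the size is generous for the binomial test. That is arithmetically right. A reader might infer from the wrong sample size that the trial is underpowered, or that it cannot detect a fall from 100% to 90%; the figures do not support either. But the 99.0% is no reassurance, since it arises because one exacerbation-free patient rejects a null that the entry criteria created.

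It is also fair to say that section 2.8 only estimates the interval and attaches no decision rule to it. The 65.3% is therefore conditional.

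Two further inferences go too far:

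- One could compute power for an analysis of exacerbation counts and call the trial weak. Section 2.4 chose a proportion, and the event rates and overdispersion needed are not in the article, so such figures say nothing about the stated plan.
- The Introduction explains the absence of a randomised control arm with the words "because of the sample size calculation considering gut microbiome diversity of individuals set as secondary endpoints". A reader might take this as a claim that 44 was derived from microbiome variability, and so as a contradiction of section 2.6. Sections 2.1 and 3 give between-person diversity as the reason for the single-arm design, and the sentence can be read in that sense. The wording is loose, but a contradiction is not shown.

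**Conclusion.** The point holds as an error in the sample-size statement. On the printed inputs the stated method gives 15, or 24 with continuity correction; the other standard forms tried range from 22 to 95 and miss 44. The swapped calculation yields 44.005, but it tests a different hypothesis and ignores the power input, so it does not rescue the claim.

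At 44 patients and a true rate of 90%, the two named analyses have 99.0% power and, under the assumed success rule, 65.3%. The stated 90% describes neither. The first figure rests on reading the binomial test as a test against the 100% fixed by eligibility, which is the natural reading of section 2.8.

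The derivation of the effect size fails separately. A rate ratio from an azithromycin-versus-placebo comparison is neither a ratio of patient proportions nor a before/after contrast. That conclusion needs no assumed event rate. None of this shows that 50 patients is the wrong number to enrol, only that the reason given for it is not valid.

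**What to change.** Keep the target of 50. In section 2.6, withdraw the statement that 44 patients are required for 90% power, and the conversion of the rate ratio of 0.9 into 90% against 100%. In their place, justify the size by precision: with 44 evaluable patients, the exact 95% confidence interval for the proportion with an exacerbation over 48 weeks has a half-width of roughly 10 points if the proportion is near 90% and 15 points if it is near 50%.

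This changes wording only; enrolment, endpoint and data collection are untouched. The price is that the stated justification becomes less favourable, since a power claim is replaced by a fairly wide interval.
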